### Randomization and allocation

In February 2015, after a 6-month pre-intervention study, hospitals were allocated randomly to either the intervention or control group. Participating hospitals were grouped into three strata corresponding to different types of hospitals: regional hospitals, district hospitals in the two largest cities (Ouagadougou and Bobo Dioulasso), and district hospitals outside those two cities. All participating hospitals were randomly allocated simultaneously to minimize the risk of allocation bias [76, 77]. To prevent imbalance regarding the level of care in each stratum, block randomization was used to generate the allocation sequence [76, 77]. Investigators were informed of the allocation just before the intervention was implemented in the intervention group.

### Data collection and processing

A data collection system has been set up in each of the 22 participating hospitals. This system is inspired by the WHO global survey on maternal and perinatal health [73], which considers both individual clinical data and organizational data at the health facility level. Information on the first 100 caesareans performed in the 6-month pre-intervention period and the first 100 performed in the 6-month post-intervention period in each hospital will be entered by local data collectors (midwives trained for this task). These midwives fill out a standard form for each eligible caesarean, which includes information on maternal characteristics, diagnosed complications, prenatal care, management of labour, caesarean indication and procedure, post-operative monitoring, and maternal and infant vital signs at discharge (see caesarean form in Additional file 11). This information will be obtained from hospital registers and from available medical records, whose quality and archiving are regularly monitored by the study coordinator. Data will be collected daily during both the pre- and post-intervention periods. With regard to organizational data and the knowledge evaluation questionnaire, the study coordinator will compile an inventory of the resources available in all the hospitals and will administer the questionnaires to health professionals before and after the intervention period.

### Data management

Midwives trained for this task will collect information on caesareans daily using a form designed for this purpose, then will enter it into a mobile telephone using Pendragon Forms VI software. The electronic forms will then be transmitted via the telephone network to a server at the trial coordination centre at the University of Montreal, where they will be stored in a secure location.

### Data quality control

The quality of clinical data will be controlled in two steps. The first consists of quarterly visits by the study coordinator, who will verify that the data collection is exhaustive by comparing the number of eligible patients from the delivery register and the hospital’s surgical protocols register with the number of patient forms completed. An additional procedure will be carried out to check that the data entered in the forms matches the data in the source documents (medical records, delivery registers, surgical registers). The coordinator will verify the quality of the data collected in each form. The completeness rate will be estimated as the proportion of forms that contain 100 % of the following information: entry date, patient identity, method of admission, reason for admission, history of pregnancy, patient’s medical history, details of the obstetric examination and labour management, indication for the caesarean, technique used for the caesarean, post-operative monitoring, date of discharge, maternal and infant vital signs at discharge. The matching rate will be estimated as the proportion of forms containing information that is consistent with the source documents. When information is missing or inaccurate on any forms, the coordinator will correct those forms from the source documents in the presence of the midwife. The corrections will be made first on the paper form and then on the electronic form. Once the corrections have been made, the database will be updated. A second check for missing or abnormal data will be performed at the coordination centre and the data collected will be updated again. If necessary, missing or inaccurate information will be added and/or corrected by communicating with the midwives by telephone. To ensure data quality, there will be regular contact with the midwives (equipped with mobile telephones), who will be given lists of duplicates and missing or abnormal data and will be responsible for correcting these errors.

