### Inclusion and exclusion criteria

A hospital was eligible for the trial if it had a functional operating room and had performed at least 200 caesareans in 2012. Twenty-two public hospitals were included in the trial between May and June 2014, out of a total of 24 eligible hospitals (91.6 %). Two university hospitals were excluded due to the high number of personnel in training. The 22 hospitals in the trial are representative of Burkina Faso’s current health system, spanning the full range in terms of context (urban versus rural), level of care (district and regional hospitals) and qualifications of health personnel. This process thus guaranteed a certain external validity of the results.

The intervention directly targets health professionals who provide obstetric care in the participating hospitals, while indirectly targeting the women giving birth there. The health professionals have been trained in the management of labour and delivery, with some also trained to perform caesareans. All health professionals involved in managing deliveries in their institutions were included in the study (*n* = 978). This total consisted of obstetricians and gynaecologists (*n* = 39), general practitioners (*n* = 32), physician anaesthetists (*n* = 3), nurses (*n* = 463), and midwives (*n* = 441). Maternity services personnel who were not involved in obstetric care in the labour room were excluded from the trial (*n* = 446).

The first 100 women with caesarean deliveries in the 22 hospitals during a 6-month period in the year preceding the intervention (May 2 to November 2, 2014) were included in the study. The first 100 women with caesarean deliveries in the 6 months following the end of the intervention will also be included. As the intervention will last 1 year, the pre- and post-intervention data collection periods will cover the same months of the year to avoid any seasonality bias. Women whose caesareans were performed in another hospital and who were subsequently transferred to a participating hospital will be excluded from the study.

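### The completeness check compares totals, but forms stop at the first 100 caesareans per hospital, so in busier hospitals a skipped case can be replaced without the totals showing it

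*Protocol article*

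**What the plan says.** Under Data quality control, the protocol article checks exhaustiveness at quarterly visits ("The first consists of quarterly visits by the study coordinator"). The coordinator is to "verify that the data collection is exhaustive by comparing the number of eligible patients from the delivery register" and the "surgical protocols register with the number of patient forms completed". That is a comparison of two totals, and the text gives no date up to which register patients are counted.

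The remaining controls in that section start from forms that already exist. There is a source check ("An additional procedure will be carried out to check that the data entered in the forms matches the data in the source documents"), and its summary measure has forms as the denominator: "The matching rate will be estimated as the proportion of forms containing information that is consistent with the source documents". The completeness rate is also a proportion of forms, and the central check looks for missing, abnormal or duplicate data in what was submitted.

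The sample is a capped consecutive series. Data collection and processing specifies "Information on the first 100 caesareans performed in the 6-month pre-intervention period and the first 100 performed in the 6-month post-intervention period" in each hospital, and Inclusion and exclusion criteria says the same. The Methods part of the Abstract instead includes every caesarean patient in the two six-month periods. A hospital was eligible if it "had performed at least 200 caesareans in 2012".

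**The concern.** Comparing totals suits a census. For a capped series, what needs checking is which 100 cases have forms. If a collector passes over one eligible caesarean and takes a later one, there are still 100 forms. No control that starts from forms can reveal a woman who has none.

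This bears on the primary outcome for three reasons.

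- **Timing.** Post-intervention cases are chosen after hospitals were allocated, by local midwives. Their hospitals have either had a year of audits, training and weekly text messages, or nothing from the project. They very probably know their arm.
- **Direction.** Under Assessment criteria, a caesarean whose criteria are undocumented, with no opposing indication, counts as non-medically indicated (NMIC). Passing over a thin file therefore tends to remove an NMIC.
- **Incentive without intent.** The completeness rate counts only forms holding all listed items, so taking a fuller file instead of a thin one improves that measure.

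If such omission were more frequent in intervention hospitals, the NMIC rate would fall with no change in practice.

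**Working it through.** **The plan's own figures.** Inputs from Sample size calculation: 100 records per hospital, intra-cluster correlation 0.02, 22 hospitals, two-sided 5%, 90% power.

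- Design effect: 1 + (100 − 1) × 0.02 = 2.98, stated as 3. It reproduces.
- Records: 22 × 100 = 2,200. It reproduces as a count.
- The section gives no control-arm rate. I assume 15%, inside the 12–24% cited in Background. Effective n per arm = 1,100 / 2.98 = 369.1. For 15% against 7.5%, z = 0.075 / √[(0.1275 + 0.0694) / 369.1] = 3.25, and power = Φ(3.25 − 1.96) = 90%. So 15% is consistent with the stated design.

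**When can a skipped case be replaced?** Months to reach 100 forms = 100 / (annual volume / 12). Hospital volumes are not given, so apart from the 200 floor these are examples.

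| Caesareans a year | In 6 months | Months to 100 | Spare cases |
|---|---|---|---|
| 200 | 100 | 6 | 0 |
| 300 | 150 | 4 | 50 |
| 400 | 200 | 3 | 100 |
| 600 | 300 | 2 | 200 |

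- At 200 a year there is no spare case: one skip leaves 99 forms against 100, and the count shows it.
- At 300 a year the three-month visit still compares running totals (about 75 expected), so a shortfall can show.
- At 400 or more the quota can be full by the first visit. A comparison of 100 eligible with 100 forms then agrees whether or not cases were skipped.
- If registers are counted to the date of the 100th form, k skips appear as 100 + k against 100 and are found.

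**Illustrative size.** Assume no true effect, a true rate p in both arms, and that every intervention hospital skips a share f of NMICs after the intervention and takes later cases under the same rule. The observed rate is q = p(1 − f) / (1 − pf). The chance of a significant result favouring the intervention is Φ(z − 1.96), with z = (p − q) / √{[p(1 − p) + q(1 − q)] / 369.1}. This normal approximation compares the arms after the intervention. With no omission it gives Φ(−1.96) = 2.5%.

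- p = 0.15, f = 0.20: q = 0.12 / 0.97 = 0.1237, a relative fall of 18%. z = 0.0263 / 0.0253 = 1.04, giving a chance of 18%. Filling 100 forms takes 100 / 0.97 = 103.1 cases, so about three skips per hospital suffice.
- p = 0.15, f = 1/3: q = 0.10 / 0.95 = 0.1053, a relative fall of 30%. z = 1.83, giving a chance of 45%.
- Over p from 0.12 to 0.24, the chance is 15% to 24% for f = 0.20 and 38% to 60% for f = 1/3.
- With only the four main indications (76% of caesareans, so 836 per arm; design effect 1 + 75 × 0.02 = 2.5), the chances at p = 0.15 are 17% and 41%.
- If only half the intervention hospitals have spare cases, the arm's rate at p = 0.15 is (0.1237 + 0.15) / 2 = 0.1369 for f = 0.20, giving a chance of 7%. For f = 1/3 it is (0.1053 + 0.15) / 2 = 0.1276, giving 14%.

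**The case against.** The strongest reply is that the text does not fix the eligible number at 100. Counting the registers to the date of the last form would expose every skip, and the article does not rule that out. Even without such a cut-off, the check works in hospitals near the eligibility floor and at any visit before the 100th form. This stands. A reader might infer that the check cannot detect selective omission at all, and the documents do not support that.

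A reader might also take the collectors to be unblinded as a stated fact. The article does not say so. It is a strong inference for the post-intervention period, and it cannot apply to baseline, which ended before the February 2015 allocation.

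The magnitude is also open to challenge. The omission shares are assumed, and they are applied to all 11 intervention hospitals and to no control. Sample size calculation also calls the intervention effective only if it brings a reduction of at least 50%. At p = 0.15 the chance that the observed fall reaches 50% is Φ{(0.5p − q) / √[(0.25p(1 − p) + q(1 − q)) / 369.1]}, which is 0.6% for f = 0.20 and 5% for f = 1/3. That is fair, but a significant Wald test would still be reported as an effect.

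Finally, register reconciliation may be detailed in a monitoring manual. That would carry more weight had the article been silent. It specifies the method, a comparison of numbers, and that method fits the every-patient sample in the Abstract better than the capped one in Methods.

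**Conclusion.** The point holds in limited form. The stated check compares totals, the other controls start from completed forms, and no stated step shows that the 100 forms are the first 100 consecutive eligible caesareans. The gap is open in hospitals clearly above 100 caesareans per six months, and widest at about 400 or more a year. How many hospitals that covers is unknown.

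The consequence is possible post-randomisation selection into the primary analysis, plausibly different by arm. The 18% (against 2.5%) is an illustration under assumed omission, not an estimate. Nothing in the article shows that omission occurs. The case for the change is that the safeguard is cheap and protects the primary outcome.

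**What to change.** Replace the comparison of totals with a patient-by-patient match:

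- At each visit, list the first 100 eligible caesareans of the period in date and time order from the surgical register, cross-checked against the delivery register.
- Match each listed case to a form by identity and date. The form already carries these ("entry date, patient identity, method of admission, reason for admission").
- Complete a form from source documents for any listed case without one, and drop any form beyond the 100th eligible case.
- Report the number of unmatched cases by arm and period.

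Also reconcile the every-patient wording in the Abstract with the first-100 rule in Inclusion and exclusion criteria and in Data collection and processing.

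The cost is a sentence or two in the quality-control procedure and modest extra coordinator time per hospital. The coordinator already visits, uses both registers and checks each form.

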### Sample size calculation

This is a superiority trial, in which the intervention will be considered effective if it leads to a reduction of at least 50 % in the NMIC rate. The sample size was calculated to maximize statistical power [78]. With an α risk of 5 % (two-sided testing) and 1-β power of 90 %, and a variance inflation factor (VIF) = 3 (calculated using an average of 100 caesareans per hospital and an intra-cluster correlation coefficient (ρ) estimated at 0.02), 2,200 caesarean records and 22 hospitals are needed.

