**Methods:**

This study combines a multicentre cluster randomized controlled trial with an implementation analysis in a mixed-methods approach. The evidence-based intervention will consist of three strategies to improve the competencies of maternity teams: 1) clinical audits based on objective criteria; 2) training of personnel; and 3) decision-support reminders of indications for caesareans via text messages. The unit of randomization and of intervention is the public hospital equipped with a functional operating room. Using stratified randomization on hospital type and staff qualifications, 11 hospitals have been assigned to the intervention group and 11 to the control group. The intervention will cover 1 year. Every patient who delivered by caesarean during a 6-month period in the year preceding the intervention and the 6 months following its end will be included in the trial. The change in the rate of non-medically indicated caesareans is the main criterion by which the intervention’s impact will be assessed. To analyze the intervention process, a longitudinal qualitative study consisting of deliberative workshops and individual in-depth interviews will be conducted. The target outcome is a 50 % reduction in the rate of non-medically indicated caesareans.

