### Hypotheses

Our main hypothesis is that clinical audits in healthcare facilities, combined with training and decision-support reminders to health professionals, will help reduce the NMIC rate by at least 50 %.

Our secondary hypotheses are that the intervention will improve: 1) health professionals’ knowledge; 2) the quality of caesareans; and 3) maternal and perinatal outcomes.

Regarding implementation, we posit that health workers will both appropriate and appreciate all three components of the intervention, and that any heterogeneity in results will be explained by the specific contexts of the different hospitals [34, 35].

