### Analysis strategy

For evaluating the effectiveness of clinical audits in reducing NMIC rates, the unit of analysis is the patient. The main tests will be intention-to-treat analyses. A first descriptive analysis will be done to verify group comparability in terms of the characteristics of hospitals and patients included in the pre-intervention period. The primary analyses will take into account inter- and intra-cluster variability. We will use generalized estimating equations (GEE) to adjust the variance estimation for the intervention’s effect on inter-dependence of the measured events (NMIC or not) among patients of the same hospital [79]. The exchangeable structure of the residual covariance matrix will be used to represent the intra-cluster correlations. The same approach will be used to test the effectiveness of CBCAs in relation to resource improvement (complexity score), medical practices (caesarean quality score), and reductions in maternal and perinatal mortality. The intervention’s effect on the NMIC rate will be estimated from the odds ratio (95 % CI) based on the GEE approach and tested with the two-sided Wald test (α = 0.05) [79]. The intervention’s effects will be evaluated systematically both without adjustment and with adjustments on the stratification variables (type of hospital) and on the other baseline characteristics selected a priori, whose distribution could, even with randomization, be unbalanced between the two groups.

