Participating hospitals were included on the basis of informed consent given by local authorities (hospital director and maternity service chief). The authorities were informed that: 1) all hospitals are free to withdraw from the project at any time; 2) the intervention will be offered in hospitals in the control group at the end of the study if proven effective; and 3) data collection will continue until the end of the study, even for hospitals that withdraw from the study. The collection of clinical data from hospital registers and medical records has been authorized by the hospital administrations and does not require patient consent [73].

All information collected on patients, health professionals, and health facilities is confidential. Access to the clinical database is restricted to the data manager until the end of the study. Access to the other databases is restricted to the researchers in charge of the study. For this study, interviews and observations will be conducted, and informed consent will be sought from all participants by means of information sheets, which they will sign. Given the variety of research activities, various types of information sheets will be developed. Consent will be certified in writing.

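### The stated success rule (a reduction of at least 50 %) is not what the planned test assesses, and the 90 % power does not apply to it

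*Protocol article*

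**What the plan says.** The Sample size calculation section opens with "This is a superiority trial" and goes on to say that "the intervention will be considered effective if it leads to a reduction of at least" 50 % in the NMIC rate. It then gives a two-sided 5 % level, 90 % power, a variance inflation factor (VIF) of 3, and a need for 2,200 records in 22 hospitals.

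The Hypotheses section repeats the threshold: the intervention "will help reduce the NMIC rate by at least 50" %. The Abstract puts it more softly: "The target outcome is a 50 % reduction in the rate of non-medically indicated caesareans".

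The Analysis strategy section estimates the effect as an odds ratio with a 95 % confidence interval, "based on the GEE approach and tested with the two-sided Wald test" at the 5 % level. It mentions no 50 % threshold. The article does not say whether 50 % applies to the point estimate, to the confidence limit, or only to planning.

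**The concern.** A superiority test asks whether the effect differs from none. A requirement of at least a 50 % reduction asks something stricter. The article states the second as its criterion for effectiveness and plans only the first. A result that is significant but short of 50 % would be a success under one section and a failure under another, and the choice between them could be made after the data are seen.

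The power statement sits in the same paragraph as the 50 % rule. A reader could take 90 % as the chance of meeting that rule when the plan's assumption is true. The scale differs too: the threshold is a fall in a rate, while the planned estimate is an odds ratio, so the result cannot be set directly against the threshold.

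**Working it through.** **Inputs.** From the Sample size calculation section: two-sided 5 %, 90 % power, 100 caesareans per hospital, intra-cluster correlation 0.02, VIF 3, 2,200 records. From the Abstract: 11 hospitals per arm, so 1,100 records per arm in one collection period. The sample size section states no baseline rate. I use 12 to 24 % from the Background as an assumed range. That figure refers to caesareans in general, whereas the primary outcome is the proportion among caesareans for the four main indications.

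**1. The plan's own figure.** VIF = 1 + (100 − 1) × 0.02 = 2.98, given as 3. For two proportions with pooled variance under the null, 15 % against 7.5 %:

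n = [1.96 × √(2 × 0.1125 × 0.8875) + 1.2816 × √(0.15 × 0.85 + 0.075 × 0.925)]² / 0.075² = (0.876 + 0.569)² / 0.005625 ≈ 371 per arm.

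The total is 2 × 371 × 2.98 = 2,211, or 2 × 371 × 3 = 2,226. So 2,200 records and 90 % power fit a test of no difference with a halved rate and a baseline near 15 %. With the same 1,100 per arm, power is 0.81 at a 12 % baseline and 0.99 at 24 %.

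**2. Where the planned test becomes significant.** Find the largest observed rate ratio r for which

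p(1 − r) / √{3 × [p(1 − p) + rp(1 − rp)] / 1,100} ≥ 1.96.

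| Control rate p | Significant at r of about | Observed reduction |
|---|---|---|
| 12 % | 0.64 | 36 % |
| 15 % | 0.68 | 32 % |
| 24 % | 0.75 | 25 % |

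Check at 24 %: 0.06 / √(3 × 0.33 / 1,100) = 0.06 / 0.03 = 2.0. An observed reduction between the last column and 50 % passes the test and fails the stated rule.

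If only 76 of each 100 records fall in the four indications, VIF = 1 + 75 × 0.02 = 2.5 and the effective size is 836 / 2.5 = 334 per arm instead of 1,100 / 3 = 367. The boundaries move to about 0.63 (12 %) and 0.74 (24 %).

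**3. Chance of meeting the 50 % rule when the true reduction is 50 %.** An estimate centred on the true value falls beyond it about half the time, whatever the baseline, correlation or sample size. A beta-binomial simulation (11 hospitals of 100 per arm, correlation 0.02, 40,000 trials) gives:

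| Baseline | Test of no difference significant | Observed reduction ≥ 50 % | Upper 95 % limit of rate ratio ≤ 0.5 |
|---|---|---|---|
| 12 % | 0.82 | 0.52 | 0.02 |
| 15 % | 0.91 | 0.52 | 0.02 |
| 24 % | 0.99 | 0.51 | 0.02 |

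To meet the point-estimate rule 90 % of the time, the true rate ratio would have to be about 0.36, 0.37 and 0.40 at these baselines, a true reduction of 60 to 64 %.

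**4. A true reduction short of 50 %.** Take a true rate ratio of 0.6 and 367 effective records per arm, with SE(log RR) = √[(1 − p₁)/(n p₁) + (1 − p₂)/(n p₂)].

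- Baseline 24 %: SE = 0.158. Power of the test is Φ(0.511/0.158 − 1.96) = 0.90. The 50 % rule is met with probability Φ(−0.182/0.158) = 0.12.
- Baseline 12 %: SE = 0.235. The same two figures are 0.58 and 0.22.

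**5. Scale.** A true halving is an odds ratio of [(p/2)/(1 − p/2)] / [p/(1 − p)] = 0.47 at 12 % and 0.43 at 24 %. Conversely, an odds ratio of 0.5 is a rate reduction of 47 % at 12 % and 43 % at 24 %. If the threshold were read on the odds ratio, it would be met in about 61 % (baseline 12 %) to 78 % (24 %) of trials with a true halving.

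Steps 2 to 4 take a simple comparison of the arms in the post-intervention period, as the 2,200 records imply. An analysis of change would move the boundaries but not remove the mismatch.

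**The case against.** The strongest defence is that the sentence is loose wording for the planning effect. It stands in the sample size paragraph, leads into alpha and power, and is the only place there that supplies an effect size. The Abstract calls 50 % a target, and the Analysis strategy section never applies a 50 % cut-off. This is plausible and keeps the remedy small. It does not remove the point, because the sentence defines when the intervention counts as effective and the main hypothesis repeats the threshold.

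Four stronger readings may tempt a reader, and the article does not support them.

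- *The 90 % power is wrong.* It is attached to two-sided testing and fits a baseline near 15 %. The one-half result holds for any threshold set at the true effect and reveals no arithmetic error.
- *Any reduction of 30 to 45 % would be clearly significant yet rejected.* At a 12 % baseline an observed 30 % reduction is not significant, since about 36 % is needed. The size of the conflict depends on the baseline.
- *Offering the intervention to control hospitals hangs on the 50 % rule.* The Discussion says that "the intervention will be offered in hospitals in the control group at the end of the study if proven effective". It does not mention 50 %, and the planned test would satisfy that wording equally well. What follows is only that the promise refers to effectiveness, which the article defines in two ways.
- *The odds ratio is the wrong measure.* It is standard for a binary outcome under GEE, and the article nowhere equates an odds ratio of 0.5 with a halved rate. Making it secondary would be a preference.

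**Conclusion.** The point holds as a conflict between two stated decision rules. It is not a matter of missing detail. The success rule in the Sample size calculation section is not assessed by the only test planned. Followed literally, it would label as not effective any significant observed reduction between about 36 % (control rate 12 %) or 25 % (24 %) and 50 %. The 90 % power belongs to the test of no difference; at a true 50 % reduction the rule is met about half the time if read on the point estimate, and about 2 % of the time if read on the confidence limit.

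The one-half figure needs no assumption beyond an estimate centred on the truth. The significance boundaries rest on 1,100 records per arm, VIF 3, a post-period comparison, and the 12 to 24 % range, which was not measured on the trial's own denominator. Neither the sample size nor the planned test is shown to be wrong.

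**What to change.** In the Sample size calculation section, replace the success sentence with: *The intervention is considered effective if the two-sided 5 % test of the primary effect rejects in favour of the intervention; a 50 % relative reduction is the effect size used for planning.* Reword the main hypothesis to match, so that it states a reduction and leaves 50 % as the planning effect.

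Because the target is a fall in a rate, also report the rate ratio and the rate difference with 95 % confidence intervals, for example by marginal standardisation from the same GEE model. The odds ratio may stay primary.

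The cost is a few sentences and two derived estimates. No new data, change in sample size or change in the planned test is needed. It should be settled before outcome data are compared by arm.
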